### Measures

A schedule of measures is shown in Table 3 and described in detail below.

Meditation practice frequency and duration will be assessed weekly. Participants will be asked how many days they practiced in the past week, the average number of sessions per day, and the average minutes per session. This is a weekly modification of the timeline followback method, which is the gold standard for reporting in substance use literature, and has been validated for exercise reporting [32] and online administration [56]. We have also validated this question format against a log of meditation timer practice data [32]. Weekly measurement supports accurate reporting in similar methods [57], while allowing us to calculate the amount of meditation each month. This will be our independent variable.

Meditation practice characteristics, including type (eg, meditation with movement such as walking meditation or mindful observation such as observing thoughts or emotions), guided versus unguided sessions (eg, “I work with a teacher or instructor” or “My practice is self-guided”), and social context of their practice (eg, “I practice in a group” or “I practice alone”), will be recorded monthly. These measures will be used to describe the sample by reporting the frequency of each practice type and context reported by participants over one year.

Secular or spiritual meditation practice will be assessed at baseline and monthly by a single item (“In the past month, what meditation traditions have you practiced in?”). Participants will be divided into 2 groups at follow-up; those who both nominated secular meditation as their tradition at baseline and reported a maximum of one month of practice in any spiritual tradition over the follow-up period, versus all participants who practiced in spiritual traditions for 2 months or more during the year. This division will facilitate investigating if those meditation practitioners who practice in spiritual traditions experience the same effects as secular practitioners, while allowing for some dabbling in different traditions by participants. This will be a covariate.

Commitment to meditation practice will be assessed at baseline with a single item (“How committed are you to practicing meditation?” Rate 1‐10). This will be a covariate.

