### Sampling Plan

#### Hypothesis 1

Sample size calculation for quality of life measured by the EQ-HWB-9 using repeated measures linear mixed modeling assumes three groups will be assessed with (1) low, (2) medium, and (3) high regular meditation dosage. Given the limited research on the effects of long-term regular meditation practice, calculating power is challenging. We have therefore used conservative power calculations that may err on the side of underestimating the power of our primary analysis but allow for use of the effect information and analytic tools that are available. We have conducted power analysis using 3 levels of variation in the predictor of monthly meditation amount, rather than the continuous variable we plan to use in our final analysis. This is to allow for the use of an analytic power calculation method for our repeated measures design, rather than simulation measures, which would be highly speculative with the limited real and independent data available for our outcome measure [64]. Ten measurement time points were also used, rather than the 12 that will be included in our analysis, as this is the maximum for GLIMMPSE (University of Florida and University of Colorado Denver) power analysis software [65].

Sample size calculation for quality of life measured by the EQ-HWB-9 using repeated measures linear mixed modeling assumes three groups will be assessed with (1) low, (2) medium, and (3) high regular meditation dosage. No increase in EQ-HWB-9 scores was predicted for the low meditation group [58]. For the high meditation group, we estimate a stepwise increase to a minimum of a 2.25-point EQ-HWB-9 increase (out of a possible 9‐45 points) from baseline to time point 5, corresponding to the change in EQ-HWB-9 from baseline to 6 months associated with improvement in mental health in a validation of the EQ-HWB-9 sensitivity to change [59]. We then predict a further 2.25-point increase to time point 10, for a total increase of 4.5 points. For the moderate meditation group, stepwise improvement was predicted with a minimum of a 2.25-point EQ-HWB-9 increase from baseline to time point 10. Baseline EQ-HWB-9 is set at 19.6, with an SD of 7.0, as per our nationally representative surveys [66]. Using GLIMMPSE [65] with 95% power and 0.05 2-tailed type 1 error rate, sample size was calculated at 435 participants. We estimated a 20% loss to follow-up over one year, bringing the sample size required to 522 participants.

#### Hypothesis 2

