For hypothesis 1, we will perform linear mixed model analysis of the fixed effect of the amount of meditation in the past month on quality of life in the past week (EQ-HWB-9), controlling for the potentially confounding baseline factors of age, caring status, education, mental health diagnosis, commitment to meditation practice, and membership of a meditation practice community at baseline. This model will allow us to assess how meditation as practiced by our participants under naturalistic conditions contributes to their quality of life, controlling for baseline differences related to time available for practice, symptom severity, motivation, and social support. If we detect an effect of meditation practice, we will perform sensitivity analysis to examine how robust this effect is to time-varying confounders by using inverse probability weighting of meditation in the last month to examine if the association would still be present if practice that month had varied independently of prior practice and benefit.

For hypothesis 2, we will perform linear mixed model analysis of the fixed effect of the amount of meditation in the past month on mental well-being in the past 2 weeks (SWEMWBS), controlling for the potentially confounding factors of age, caring status, education, mental health diagnosis, commitment to meditation practice, and active membership of a meditation practice community at baseline. If we detect an effect of meditation practice, we will again perform time-varying confounding sensitivity analysis with inverse probability weighting.

For hypothesis 3, we will add the variable capturing whether participants practiced secular meditation traditions (with no more than one month of reported practice in a spiritual tradition) versus engaging in spiritual traditions and its interaction term with the amount of meditation to the model for hypothesis 1. This initial analysis will allow us to assess whether predominantly secular meditation has a differential effect from meditation that incorporates spiritual practices, as practiced in real-life contexts, while retaining sufficient power. If we detect an effect, we will perform further exploratory analysis into what may be driving this difference. We will also describe the groups in terms of meditation practice characteristics, including proportion of practice types and social context.

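### The secular/spiritual moderator for Hypotheses 3 and 4 is built from reports over the whole follow-up, so later behaviour labels earlier outcomes, and its two groups do not cover everyone

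*Protocol article*

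**What the plan says.** In the Protocol article, Measures, the item on tradition is collected repeatedly: "Secular or spiritual meditation practice will be assessed at baseline and monthly by a single item". The grouping comes later: "Participants will be divided into 2 groups at follow-up". The secular group is "those who both nominated secular meditation as their tradition at baseline and reported a maximum of one month of practice in any spiritual tradition" over follow-up. It is set against the spiritual group: "versus all participants who practiced in spiritual traditions for 2 months or more during the year". The reason given is to tolerate brief trials of another tradition.

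The Analysis Plan enters this as one variable per person. For Hypothesis 3 it adds the variable and "its interaction term with the amount of meditation to the model for hypothesis 1"; Hypothesis 4 does the same with the Hypothesis 2 model. There the contrast is between participants who "practiced secular meditation traditions (with no more than one month of reported practice in a spiritual tradition) versus engaging in spiritual traditions". The requirement of a secular baseline nomination is not repeated.

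The Analysis Plan handles missing outcomes by REML under missing at random. It adds censoring weights for the primary analysis, and weighting for time-varying confounding under Hypotheses 1 and 2. Neither form of weighting is described for Hypotheses 3 and 4.

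**The concern.** A moderator should be fixed before the outcomes it is used to explain, or updated from information that precedes each of them. This one is neither. A secular starter who takes up spiritual practice in months 9 and 10 is coded spiritual for months 1 to 8 as well. If people take it up because meditation has been going well, or badly, the group label carries information about the outcome. The practice-by-group interaction can then differ from zero with no effect of tradition. The plan already recognises this kind of feedback, since it weights for practice that depends on earlier practice and benefit under Hypotheses 1 and 2.

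The label also depends on staying in the study and on continuing to meditate. Someone who returns no report or one report can never reach two spiritual monthly reports. Someone who stops meditating but keeps answering gains no further spiritual months. A secular starter who stops stays in the secular group, while a spiritual starter who stops early may belong to neither. Low-practice months, which the interaction slope needs, can therefore be lost from one side only.

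Table 1 would read a significant interaction as practice within a spiritual tradition having a larger or smaller effect. Selection by switching or persistence could produce the same result. REML does not help, because it addresses missing outcomes and not a covariate built from post-baseline reports.

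**Working it through.** **1. Do the two groups cover everyone?** Applying the Measures rule to each combination:

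| Baseline tradition | Spiritual months reported in follow-up | Group (baseline month not counted) | Group (baseline month counted) |
|---|---|---|---|
| Secular | 0 or 1 | Secular | Secular |
| Secular | 2 or more | Spiritual | Spiritual |
| Spiritual | 0 | Neither | Neither |
| Spiritual | 1 | Neither | Spiritual |
| Spiritual | 2 or more | Spiritual | Spiritual |

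Both columns are shown because the secular rule counts months over the follow-up period and the spiritual rule counts months during the year, while the baseline item covers the preceding month. Under either reading at least one cell has no group.

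**2. How does the label depend on reports returned?** Take a secular starter who returns m monthly reports, each showing spiritual practice with probability p, independently. The values of p and the independence are assumptions; the article gives no switching rate.

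P(classed spiritual) = P(2 or more of m) = 1 − (1−p)^m − m·p·(1−p)^(m−1).

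For p = 0.10 and m = 12: 1 − 0.282 − 0.377 = 0.341.

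| p | 3 reports | 6 reports | 12 reports |
|---|---|---|---|
| 0.05 | 0.007 | 0.033 | 0.118 |
| 0.10 | 0.028 | 0.114 | 0.341 |
| 0.20 | 0.104 | 0.345 | 0.725 |

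At every rate the probability rises steeply with length of follow-up.

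**3. How many spiritual starters does dropout alone leave unclassified?** The Sampling Plan gives the loss: "We estimated a 20% loss to follow-up over one year, bringing the sample size required to 522 participants". (The 522 is 435 × 1.2; nothing below uses it.) Spread evenly over 12 months as a constant hazard, the monthly loss is h = 1 − 0.8^(1/12) = 0.0184. Assume spiritual practice in 90% of reported months.

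Baseline month not counted (0 or 1 spiritual months is unclassified):
- lost before any report: 0.0184 × 1 = 0.0184
- lost after one report: 0.0181 × 1 = 0.0181
- lost after two reports: 0.0178 × 0.19 = 0.0034
- lost after three reports: 0.0174 × 0.028 = 0.0005
- total: 0.0404, about 4%.

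Baseline month counted (only 0 is unclassified):
- 0.0184 + 0.0181 × 0.10 + 0.0178 × 0.01 = 0.0204, about 2%.

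**4. How much data do they carry?** Table 3 records practice amount weekly and not at baseline, so a person with no monthly report has no practice–outcome pair. That is 0.0184 of the 0.0404. The others contribute mostly one row each. Expected unclassified rows are about 0.0181 × 1 + 0.0034 × 2 + 0.0005 × 3 = 0.026 per spiritual starter, against about 10.7 rows expected overall under the same hazard. That is roughly 0.2%.

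This covers dropouts only. People who stop meditating but keep answering can supply up to 12 rows, and their number cannot be worked out from the article.

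**The case against.** The question as posed concerns practice over the year: whether it stays predominantly secular or takes in spiritual practice. Baseline tradition alone would answer a different question, and if switching is common it would code many people who practised spiritually as secular (34% of secular starters with all 12 reports at the assumed 10% rate). This stands, and is a reason not to make baseline tradition the only analysis.

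The unclassified dropouts carry little data and the monthly rates are assumed. Tradition is also likely to persist from month to month, which the independent-months calculation ignores. This stands too. The percentages are illustrations, and the unclassified share is not the main issue.

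A reader might infer that the Analysis Plan puts early dropouts who began in a spiritual tradition into the secular group. The text does not establish that. The limit in "with no more than one month of reported practice in a spiritual tradition) versus engaging in spiritual traditions" can be read as qualifying only people who practised secular traditions, as shorthand for the rule in Measures. The wording is ambiguous about where these people go.

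A reader might also suppose that loss is concentrated in the first two months, leaving far more people unclassified. The article gives no such pattern, and it recruits people past initial instruction partly because dropout is common in the first weeks of practice.

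Finally, handling of missing months could be left to a fuller analysis plan. That does not dispose of the point: the article itself fixes the grouping rule, and that rule uses future reports and leaves a gap.

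**Conclusion.** The concern holds. As fixed in Measures, the moderator uses behaviour that comes after many of the outcomes it is meant to explain, and it depends on reports returned and on continued practice. The two groups are not exhaustive: a spiritual starter with no follow-up spiritual month (or with none or one, if baseline is not counted) has no place.

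The dependence on follow-up length is clear in direction, but its size rests on assumed rates: for a secular starter, about 12% to 34% classed spiritual after 12 reports at monthly rates of 5% to 10%, against about 1% to 3% after 3. Dropout alone leaves about 2–4% of spiritual starters unclassified, assuming even loss and 90% spiritual months. These people supply few rows, so the weight of the concern lies on future-defined labelling and the tie between label and continued practice. The actual bias in the interaction cannot be computed, because the article gives no mix of traditions and no switching rate.

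This should be fixed. It affects only Hypotheses 3 and 4; the primary analysis does not use the variable.

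**What to change.** 1. Write one exhaustive definition and use it in both Measures and the Analysis Plan. For example, place anyone who names a spiritual tradition at baseline in the spiritual group, along with secular starters who later report two or more spiritual months. State whether the baseline month counts.
2. Prespecify analyses of Hypotheses 3 and 4 in which the moderator uses only information available before each outcome: one with baseline tradition, and one time-updated with tradition reported up to the previous month.
3. State that an interaction will be interpreted as an effect of tradition only if it holds in these analyses.
4. If the two-month rule is kept because the question is about practice over the year, say so, and describe its result as an association with practice pattern.

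Table 3 already schedules the tradition item at baseline, monthly and at one year, so no new data are needed. The cost is some wording and extra analysis. Switchers will dilute the baseline contrast, perhaps considerably if switching is common, which is why the time-updated version should sit beside it.

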### Participant Verification

The study uses a combination of methods to both discourage nongenuine participants and to verify that those participants who are recruited are genuine. Entry into the study involves 4 Qualtrics surveys delivered on consecutive days, followed by download of the app Fabla, which is restricted to Australia, New Zealand, the United Kingdom, or the United States, before commencing the weekly survey schedule, as shown in Table 3. The first expression of interest survey will exclude participants who fail Qualtrics internal bot checks and who are detected to be outside our recruitment countries. The second survey will repeat date of birth questions from the expression of interest to detect inconsistent responses.

**Table 3. T3:** Schedule of measures.

Measures	Baseline	Weekly	Monthly	1 year
Outcome measures				
Health and well-being (EQ-HWB-S^a^)	✓		✓	✓
Mental well-being (SWEMWBS^b^)	✓		✓	✓
Independent variables				
Meditation practice frequency and duration		✓		
Meditation practice characteristics	✓		✓	✓
Secular or spiritual practice tradition	✓		✓	✓
Covariates				
Meditation history	✓			
Sociodemographics	✓			
Physical and mental health status	✓			✓
Other variables				
Cost of meditation practice	✓		✓	✓
Cost of mental health care use	✓		✓	✓
Meditation-related adverse effects scale (MRAES)	✓		✓	✓

a EQ-HWB-S: EQ Health and Wellbeing—Short version.

b SWEMWBS: Short Warwick-Edinburgh Mental Well-Being Scale.

After we have received 7 separate survey responses from participants, their IP and internet service provider (ISP) will be inspected. This IP inspection identifies participants whose IP addresses change on each survey, which indicates possible “residential proxy” use, those who have IP addresses associated with a known virtual private network (VPN), those who have more than 2 ISPs associated with their IPs, and those who have IP addresses associated with a data center (eg, Amazon Web Services).

Participants who are identified by these IP inspections will be manually screened by listening to voice recordings they will provide in Fabla. Those participants who we are not able to verify through this process will be contacted and offered an online interview. Prospective participants who do not respond after follow-up, refuse an interview or alternative contact method, or are suspected to be nongenuine during an interview will be considered nongenuine, excluded from further participation, and have their data removed.

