Community of practice membership will be assessed by a single item and recorded at baseline and one year (“Are you an active member of a community of practice [eg, sangha, meditation group, or online communities]? Yes/No”). This will be a covariate.

Age in years will be recorded at baseline. This will be a covariate.

Caring status, including type of caring relationship, will be assessed at baseline. This will be a covariate.

Education will be assessed by a question asking, “What is the highest level of education you have completed?” and will be recorded at baseline. This will be a covariate.

Mental health diagnosis will be assessed by a single item at baseline (“Have you ever been diagnosed with a mental illness by a clinician?” Yes/No/Prefer not to say). This will be a covariate.

The cost of meditation practice will be assessed through self-reported questions asking participants whether they have spent any money related to their meditation practice, including on classes, courses, retreats, smartphone apps, resources such as mats, books, and clothes, and donations to meditation teachers or centers. These questions will be asked at baseline, monthly, and one year later.

The cost of mental health care use will be assessed via questions on type, frequency, and costs of psychological support. Specifically, participants will be asked, “In the past month, how many times did you see a… psychologist, psychiatrist, social worker, counselor, or other.” Participants will then be asked how they paid for this mental health service use (eg, “Out-of-pocket” and “Publicly funded”) and their out-of-pocket expenditure on mental health services in the past month. These questions will be asked at baseline, monthly, and one year. This will be used in the economic evaluation.

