The study also aims to conduct an economic evaluation in the form of an exploratory cost-effectiveness analysis to investigate costs and outcome comparisons associated with regular meditation practice. As this study is a cohort study and not an RCT where we would usually see cost-effectiveness analysis conducted, and as there is no control group, we plan to construct an exploratory cost-effectiveness analysis using a comparator group of those not continuing to meditate. This is a major limitation to the cost-effectiveness analysis proposed in this study.

There are further limitations regarding effects and costs. Although the EQ-HWB-9 has been shown to be valid for measuring quality of life in people who meditate [76], there are currently no country-specific value sets for the EQ-HWB-9 for Australia, New Zealand, or the United States. We will have detailed information on costs due to psychological care; however, we will need to estimate costs from this information for the relevant country’s health systems where costs are not out-of-pocket. This analysis is further exploratory on the basis of the direction of the effect. For instance, if, through partaking in meditation practice, participants decide to pursue mental health support, this will increase costs but may also increase outcomes. Hence, lowering mental health support costs may not be the objective here. We acknowledge the potential opportunity cost of meditation practice, and while we will be able to provide information on the time commitment needed to achieve benefit in our primary analysis, we are unable to address this in the current exploratory cost-effectiveness analysis. As the outcomes look at change in QALYs over one year, we will also not be able to take into account changes in effects and costs during this period for the base analysis. We may be able to do further exploratory analysis investigating the associations between costs and effects over time in a future study.

Finally, the study aims to estimate the incidence of MRAEs. We anticipate the incidence of MRAEs will be around 10%, in line with previous research [42]. We also expect the average impact on daily function to be small, on average, but that some participants will experience significant impairment to daily function. We plan to conduct a future mixed methods examination of MRAEs to explore their predictors and phenomenology.

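### Mental health service use is recorded monthly but has no stated role outside costing, so care that starts or stops alongside practice could confound the meditation coefficient

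*Protocol article*

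**What the plan says.** The Measures section asks about "type, frequency, and costs of psychological support", including the number of visits in the past month to a psychologist, psychiatrist, social worker, counselor or other provider. On timing it says "These questions will be asked at baseline, monthly, and one year". On purpose it says "This will be used in the economic evaluation". The neighbouring items on community membership, age, caring status, education and diagnosis are each labelled a covariate. Table 3 lists "Cost of mental health care use" under other variables, not under covariates.

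The Analysis Plan fits the hypothesis 1 model "controlling for the potentially confounding baseline factors of age, caring status, education, mental health diagnosis, commitment to meditation practice, and membership" of a practice community. Hypothesis 2 uses the same six factors. Hypotheses 3 and 4 add only tradition and its interaction with practice. The closest item to treatment is the diagnosis question, "Have you ever been diagnosed with a mental illness by a clinician".

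For hypotheses 1 and 2, if an effect is detected, an inverse-probability-weighted sensitivity analysis for time-varying confounders follows. It asks whether the association would remain "if practice that month had varied independently of prior practice and benefit".

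The Discussion, on the limits of the economic analysis, notes that "if, through partaking in meditation practice, participants decide to pursue mental health support, this will increase costs but may also increase outcomes". Table 1 reads a significant coefficient as practice increasing or decreasing quality of life.

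**The concern.** Participants may start, change or stop mental health care during the year. Such care is aimed at much the same outcomes as EQ-HWB-9 and SWEMWBS measure. If it starts or stops for its own reasons and practice moves with it, the practice coefficient carries part of the effect of care.

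The bias could go either way. It would flatter meditation if care improves outcomes and also encourages practice. It would hide a benefit if people take up both care and practice when they feel worse.

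A lifetime diagnosis recorded once at baseline cannot show whether someone is in treatment now, or begins or ends it later. The information that could show this is already being collected.

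**Working it through.** **Role of the variable.** No stated figure is in dispute, so the first check is to trace every place that gives mental health care use a role.

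| Place | Role of mental health care use |
|---|---|
| Measures | Economic evaluation |
| Table 3 | Listed under other variables |
| Table 1 and Analysis Plan, hypotheses 1 and 2 | Not among the six baseline covariates |
| Analysis Plan, hypotheses 3 and 4 | Not added |
| Analysis Plan, weighting analysis | Not named; weight predictors are not listed |
| Analysis Plan, aim 5 | Cost component |

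**Illustrative size.** The formula for omitted-variable bias per SD of practice is

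bias = b × p(1−p) × d / (1 + p(1−p)d²),

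where b is the effect of care in points, p the share of person-months in care, and d the extra practice in care months in SD units. Points are counted in the direction that the Sampling Plan treats as improvement.

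- From the Sampling Plan: b = 2.25 points. This is the EQ-HWB-9 change linked there to improved mental health, borrowed here as the effect of care.
- Assumed, because the documents do not give them: p = 0.10 to 0.30 and d = 0.1 to 0.5.

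Results:
- p = 0.10, d = 0.1: 2.25 × 0.09 × 0.1 / 1.0009 = 0.02 points
- p = 0.20, d = 0.3: 2.25 × 0.16 × 0.3 / 1.0144 = 0.11 points
- p = 0.30, d = 0.5: 2.25 × 0.21 × 0.5 / 1.0525 = 0.22 points

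A second set of assumptions drops the small denominator term and takes p = 0.1 to 0.2, a care effect of 0.2 to 0.7 SD, and d = 0.2 to 0.4.
- Low end: 0.09 × 0.2 × 0.2 = 0.0036 SD; × 7.0 = 0.03 points
- High end: 0.16 × 0.7 × 0.4 = 0.0448 SD; × 7.0 = 0.31 points

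For scale, the Sampling Plan assumes gains of 0, 2.25 and 4.5 points by the last time point. That averages about half over the year, or 1.125 points per dose step. With equal thirds (also assumed) the gradient is 1.125 × √(2/3) = 0.92 points per SD of practice.

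**Effect on the test.** A random-intercept model was simulated with 435 participants, 12 months, SD 7.0, no true meditation effect, b = 2.25, within-person correlation 0.5 or 0.7 (assumed), and 600 replicates per setting. The six baseline covariates were not simulated.

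| Setting | Spurious coefficient, care omitted | Rejection at nominal 5%, care omitted |
|---|---|---|
| d = 0.1, all p | 0.02 to 0.05 | about 5% to 10% |
| p = 0.20, d = 0.3 | about 0.12 | 23% (correlation 0.5), 36% (0.7) |
| p = 0.30, d = 0.5 | about 0.23 | 65% (0.5), 86% (0.7) |

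With same-month care in the model, the coefficient was about 0 and rejection was 3% to 7%. That shows what omission can do; it is not a test of the lagged remedy proposed below.

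**If care is a mediator.** With a true direct effect of 0.50, p = 0.20, d = 0.3 and correlation 0.6, the unadjusted model gave 0.69, the total effect. Adjusting for same-month care lowered it to 0.51. Plain adjustment for same-month care would therefore remove part of what the study wants to estimate.

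**The case against.** Three objections have force.

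- **The weighting analysis.** A reader might infer that the plan shuts mental health care out of every effect analysis. The documents do not support that. The Analysis Plan announces weighting for time-varying confounders and describes the question it answers, but it does not list the weight predictors. Such a list may sit in an analysis plan not shown. Measures states one use of the data without saying it is the only one. If prior benefit enters the weights, it also carries part of any earlier effect of care. What remains is that care is not named, that the analysis runs only after an effect is found (so it cannot uncover a masked one), and that the primary estimate does not change.
- **The Discussion sentence.** A reader might infer that the protocol itself concedes confounding. It does not. The sentence describes meditation leading people to seek care, and on that path the benefit belongs to meditation's total effect. The confounding path, in which care starts or stops for other reasons, is not stated anywhere. Nothing in the design excludes it.
- **Size.** A reader might infer that the meditation effect will be overstated by a known amount. The share of months in care and the link between care and practice have no source in the documents, and the direction is open. With weak co-movement the test stays near its nominal level.

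**Conclusion.** The point holds in limited form. Monthly treatment data exist and are given a role only in costing. The listed covariates capture a lifetime diagnosis but not treatment, and the weighting analysis does not name care. Care that changes for reasons other than meditation could therefore confound a coefficient that is read causally.

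The possible bias is about 0.02 to 0.3 EQ-HWB-9 points per SD of practice, against an assumed planned gradient of about 0.92. The top of that range needs all the inputs at their maximum together, and the sign may be positive or negative. With strong co-movement even a small bias can push the false-positive rate well above 5% at this sample size. With weak co-movement it matters little.

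This is a cheap improvement to consider, not a demonstrated error.

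**What to change.** 1. Add baseline mental health service use to the covariates for hypotheses 1 to 4, in the Analysis Plan and in Table 1.
2. Name prior-month mental health visits, as reported at the previous survey, as a predictor in the inverse-probability weights. Run that analysis for hypotheses 1 and 2 whatever the primary result. Placing prior-month care in the weights deals with it as a confounder without adjusting away care caused by earlier meditation.
3. Optionally, report hypotheses 1 and 2 with and without lagged service use as a sensitivity analysis.

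Do not condition the primary model on same-month care. Do not describe the coefficient as interpreted given concurrent care: neither the lagged approach nor the unadjusted model supports that reading.

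The cost is some wording and a little more modelling, with no new data. The lagged-covariate model in step 3 may attenuate part of the mediated pathway, which is why it is reported next to the unadjusted result. Care and practice that change within the same month would remain only partly controlled.
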